# Protocol for the melatools skin self-monitoring trial: a phase II randomised controlled trial of an intervention for primary care patients at higher risk of melanoma

**DOI:** 10.1136/bmjopen-2017-017934

**Published:** 2017-11-28

**Keywords:** melanoma, skin cancer, randomised controlled trial, risk-stratified, primary care

## Abstract

**Introduction:**

Melanoma is the fifth most common cancer in the UK. Incidence rates have quadrupled over the last 30 years and continue to rise, especially among younger people. As routine screening of the general population is not currently recommended in the UK, a focus on secondary prevention through early detection and prompt treatment in individuals at increased risk of melanoma could make an important contribution to improve melanoma outcomes. This paper describes the protocol for a phase II, multisite, randomised controlled trial, in the primary care setting, for patients at increased risk of melanoma. A skin self-monitoring (SSM) smartphone ‘App’ was used to improve symptom appraisal and encourage help seeking in primary care, thereby promoting early presentation with skin changes suspicious of melanoma.

**Methods and analysis:**

We aim to recruit 200 participants from general practice waiting rooms in the East of England. Eligible patients are those identified at higher melanoma risk (using a real-time risk assessment tool), without a personal history of melanoma, aged 18 to 75 years. Participants will be invited to a primary care nurse consultation, and randomised to the intervention group (standard written advice on skin cancer detection and sun protection, loading of an SSM ‘App’ onto the participant’s smartphone and instructions on use including self-monitoring reminders) or control group (standard written advice alone). The primary outcomes are consultation rates for changes to a pigmented skin lesion, and the patient interval (time from first noticing a skin change to consultation). Secondary outcomes include patient sun protection behaviours, psychosocial outcomes, and measures of trial feasibility and acceptability.

**Ethics and dissemination:**

NHS ethical approval has been obtained from Cambridgeshire and Hertfordshire research ethics committee (REC reference 16/EE/0248). The findings from the MelaTools SSM Trial will be disseminated widely through peer-reviewed publications and scientific conferences.

**Trial registration number:**

ISCTRN16061621.

Strengths and limitations of this studyThe MelaTools Skin Self-Monitoring (SSM) Trial is among the first, in the UK or internationally, to risk stratify the primary care population in order to target an intervention to improve timeliness of melanoma detection.It uses digital technology to encourage people at higher risk of melanoma to self-monitor their skin and present to their physician with any concerns.The trial aims to establish the feasibility and acceptability of undertaking SSM among people at higher risk of melanoma; it will also report on consultation rates and includes 6-month and 12-month participant follow-up.As this is a feasibility trial, the main limitation is that the small sample size will limit meaningful interpretation of the clinical outcomes; furthermore, the sample may not be fully representative of the UK adult population as it excludes people who do not own a smartphone, and those with physical disorders severe enough to hamper smartphone use.Information from this trial will enable planning of a larger phase III trial to further assess the impact of the use of a smartphone App to encourage SSM on clinical outcomes for melanoma.

## Introduction

Malignant melanoma is the leading cause of skin cancer deaths in the UK with 2459 in 2014.^1^ Melanoma skin cancer incidence has quadrupled over the last 30 years, and continues to rise.^2^ Although melanoma is more common with increasing age, around half of melanoma in the UK each year are diagnosed in people aged <65.^3 4^ Risk factors include fair skin, family history of melanoma, multiple naevi and sun damage. Melanoma is associated with significant morbidity, and the thickness of the lesion at diagnosis is the most important prognostic factor: stage 1 disease has 5-year survival rates of over 95%, compared with <25% for stage 4 disease.^5^ The UK has lower 1-year and 5-year melanoma survival rates than comparable countries in Europe.^6^ Diagnostic delays are thought to contribute to this, and there is evidence of avoidable delay.^7^ Evidence from the SCREEN project in Germany, conducted between 2003 and 2004, suggested that population screening may have an impact on melanoma incidence and 5-year mortality.^8 9^ However, this evidence is controversial, and routine screening of the general population is not currently recommended anywhere worldwide, although some countries (Australia, New Zealand, Germany, the Netherlands and the UK) recommend regular skin checks and/or self-examination for certain subsets of patients at increased risk of melanoma.^10^ Therefore, a focus on targeted population screening could make an important contribution to melanoma outcomes through early, timely detection and prompt treatment.

Patient pathways to presentation and management in primary care are key determinants in cancer outcomes. When compared with people diagnosed with other cancers, those diagnosed with melanoma have the second longest median time between first noticing a symptom and presenting to primary care (patient interval).^11 12^ The patient interval could potentially be reduced by providing patients with clear information on the signs and symptoms of melanoma and guidance on monitoring skin changes,^13^ through community campaigns such as the Be Clear on Cancer skin cancer campaign.^14^ More targeted approaches could focus on individuals at higher risk.

Smartphones offer considerable potential to promote earlier presentation by people with cancer, including melanoma.^15^ More than 70% of the UK adult population now own a smartphone (Techtracker), and there are many smartphone applications (‘Apps’) focusing on health issues, presenting new opportunities for risk assessment, symptom appraisal, monitoring symptoms and signs over time, and cues to seek professional advice. Furthermore, up to 75% of melanomas are detected by people or their family/friends, rather than healthcare professionals. To maximise the effectiveness of skin self-monitoring (SSM), the person performing the examination should be able to identify skin changes and features of skin lesions which could indicate melanoma, yet recent studies have demonstrated that suspicious signs of skin cancer may not be widely known.^13 16^ Important international evidence has shown that it is possible to educate patients and the public: newly diagnosed Italian melanoma patients who performed self-skin examination were found to have thinner tumours,^17^ and Australian patients with melanoma were found to adhere to medical advice on skin self-examination during follow-up care.^18^ A recent Scottish study has demonstrated that patients with melanoma are prepared to use digital technology to support them in conducting SSM during follow-up.^19^ We therefore set out to explore using mobile technology for SSM among people at higher risk of melanoma in the primary care setting to encourage timely consultation for possible melanoma.

### Preliminary phase I research

Guided by the Medical Research Council framework on developing and evaluating complex interventions,^20^ three phase I studies were conducted to (1) assess the feasibility and acceptability of defining a population at higher risk of melanoma from UK general practice; (2) review the availability of suitable smartphone SSM Apps and (3) pilot the intervention.

#### Assessing the feasibility and acceptability of defining a population at higher risk of melanoma from UK general practice

The MelaTools-Q Study findings have already been reported.^21^ Briefly, 7742 patients (86% of those approached) were recruited from the waiting rooms of 22 general practices in three UK regions: Eastern England, Northeast Scotland and North Wales. Using tablet computers, they completed an electronic questionnaire incorporating the Williams melanoma risk prediction model,^22^ including items relating to seven risk factors: gender, age, natural hair colour at age 15, number of severe sunburns aged 2–18, prior non-melanoma skin cancer, number of raised moles on both arms and density of freckles on both arms before age 20. The study showed that, after weighting to the age and sex distribution, the lower and upper quartile cut-offs used by Williams *et al*, 25 and 34, would allow between 4% and 20% of the population to be identified as higher risk, and those groups would contain 30% and 60%, respectively of individuals who would develop melanoma. Therefore, real-time risk assessment for melanoma in UK primary care is both feasible and acceptable.

#### Reviewing the availability of suitable smartphone SSM Apps

Our initial review, conducted in July 2014, identified 39 smartphone Apps available from Apple and Android App online stores.^23^ However, when the same search strategy was re-run in September 2015, eight new SSM Apps were identified, while eight of the previously identified SSM Apps were no longer available. Among the 39 newly identified SSM Apps, 11 were not available in both Apple and Android App stores; 10 did not include a monitoring function; 5 did not include photography of skin lesions; 5 had poor functionality; 2 were not available in England; 2 were classified as medical devices; 1 was under development, 1 one had no reminder feature, deemed vital for monitoring functionality. Two SSM Apps were considered potentially most suitable to include in the intervention (see figure 1).

**Figure 1 F1:**
[figure not shown]
The availability and suitability of smartphone skin self-monitoring (SSM) Apps for the MelaTools SSM Trial.

#### Piloting the intervention

Qualitative research, using focus groups and interviews, was conducted with individuals at increased risk of melanoma to provide in-depth understanding of consumer views on the usefulness and usability of the two selected SSM Apps. Eight people at increased risk of melanoma were recruited for two focus groups from a local melanoma patient support group; three of their relatives also took part. People were also recruited in the waiting rooms of two suburban general practices and completed the Melatools-Q risk assessment tool.^21^ Five identified to be at increased risk of melanoma were invited to participate in two other focus groups. A total of 16 participants tested at least one of the SSM Apps. The participant characteristics are shown in table 1.

**Table 1 T1:** Piloting the intervention–consumer characteristics

	Participants (n=16)
Risk of melanoma	
High risk of melanoma (treated melanoma)	8
At above population risk	5
Unknown risk (relative of high risk participant)	3
Gender	
Male	8
Female	8
Age	
<35 years	2
36–44 years	1
45–54 years	3
55–64 years	7
65–74 years	3
Ethnicity	
White British	15
White other	1
Education (highest qualification)	
GCSE or equivalent*	1
A level or equivalent†	3
Vocational	2
Undergraduate degree	3
Postgraduate degree or professional qualification	7
Employment status	
Student	1
Work part time	5
Work full time	4
Homemaker	1
Retired	5
Index of Multiple Deprivation quintiles	
Least deprived 1	8
2	5
3	2
4	0
Most deprived 5	0
Unknown	1

*GCSE, an academic qualification awarded in a specified subject, generally taken in a number of subjects by pupils aged 14–16 in England and Wales.

†A level, same, generally taken aged 16–18.

GCSE, General Certificate of Secondary Education.

The four focus groups were conducted by an experienced qualitative researcher (KM) and research assistant (RL), either at the recruiting general practice or university premises; each lasted approximately 90 min, was audiorecorded and the recordings transcribed verbatim. Each participant was initially helped to load the two SSM Apps on their smartphones, and given time to familiarise themselves with their use. Thematic analysis^24^ showed that, overall, participants in all four groups and at all strata of increased risk of melanoma felt that using a SSM App would be helpful and achievable. Many felt that using a SSM App would enhance their current SSM habits: *‘*I look at the moles and I just keep an eye on them*’ (Male, above-population risk, group 3).* Many also felt that using a SSM App could help reduce their worry about developing skin cancer: *‘*cos my dad had cancer recently so [my mother] says we’re at a higher risk, so she goes on about that*’ (Female, above-population risk, group 4).* Some felt that using a SSM App would guide their help-seeking behaviour for skin changes or moles: ‘It’s that knowledge, if it’s, you know, three months, whatever it is, if you can actually say look there is a visible change then you’re getting a bit of information that they probably could do with…you’ve got physical evidence, and then the confidence to go to…’ (Male, above-population risk, group 4). Several also commented on additional features on smartphones which might help prevent development of future melanomas: ‘I’ve got a UV index on my phone so I can always check what that is, so putting sun cream on.’ (Male, high risk, group 2).

The five participants recruited via primary care were invited to complete a diary 1 and 2 months later, and then participate in a telephone interview after the third month. Diary records and thematic analysis of the interviews (as above) confirmed that participants used many features of both SSM Apps, including taking photographs, mapping these to body parts, comparing photographs over time and using the analysis function (available in only one of the Apps). There was unanimous agreement between participants about the App which was easier to use (MySkinPal), and most reported that they would continue to use it after the study, particularly as they found the App’s notifications the most efficient method to prompt them to complete future SSM. Despite this, several also reported that they found taking photographs quite challenging, and that they had to recruit a family member to assist them in taking photographs to compare skin changes over time. Furthermore, while regularly self-monitoring their skin during the study, most participants reported worrying about skin cancer ‘sometimes’, seeking further information about skin changes or moles via the internet, speaking to friends and family, and visiting their general practice.

In conclusion, this preliminary phase I work enabled consumer choice of the more user-friendly SSM App, resulted in modifications to the language used in the trial consultation and led to the development of the MelaTools SSM Trial.

The trial aims to assess the effect of using an SSM App compared with standard information about detecting skin cancer on consultation rates and the patient interval (the time from first noticing a skin change/mole to consultation with a primary care healthcare professional) among patients at increased risk of melanoma, identified via primary care. In addition, to obtain preliminary estimates of effect across a range of outcome measures to inform selection of the primary outcome for a definitive phase III trial. We hypothesise that primary care patients at higher risk of melanoma will seek help more rapidly after noticing skin changes when using an SSM App compared with using standard written information.

## Methods and analysis

### Study design and setting

The phase II trial is a multisite randomised controlled trial (figure 2), set in 11 general practices across Eastern England. Those who meet the eligibility criteria and consent to participate are randomised 1:1 into either the control or intervention group. Randomisation is being performed using an online system provided by the Clinical Trials Unit based at Kings College London.

**Figure 2 F2:**
[figure not shown]
MelaTools Skin Self-monitoring (SSM) Trial flowchart.

### Study participants

#### Eligibility criteria

Eligible participants are individuals aged between 18 and 75 years who own a smartphone (Apple or Android), and, on completion of the Melatools-Q risk assessment tool,^21^ are found to be at increased risk of melanoma. Participants are able to read and write English and to give informed consent.

#### Exclusion criteria

Exclusion criteria are previous diagnosis of melanoma, severe psychiatric or cognitive disorders, or a physical disorder severe enough to inhibit the use of a smartphone.

#### Participant recruitment

Potentially eligible individuals are approached by research nurses or research assistants in GP waiting areas at different times of the day and different days of the week, in order to ensure that a broad range of ages, gender and educational level are approached. Those meeting initial screening criteria are given a tablet computer that includes a short version of the participant information sheet and an online consent form agreeing to have their risk assessed and be considered for the trial. They complete the MelaTools Q study risk assessment tool^21^ which stratifies respondents into ‘population risk’ (majority) and ‘increased risk’, using a cut-off score in the Williams model of 25. People at ‘population risk’ are thanked and given the Cancer Research UK leaflets on risk factors of melanoma and melanoma detection advice. People at increased risk are invited to participate in the trial, and given the full-length trial Participant Information Sheet and an appointment time within 14 days for the primary care nurse trial consultation. Individuals not wishing to take part are asked their reason for declining.

#### Control and intervention groups and randomisation

Informed written consent is obtained from all participants at the start of the trial consultation (online supplementary file S1). After completion of a baseline questionnaire, the trial nurse guides the participant through the Cancer Research UK leaflets on ‘Be SunSmart cut your cancer risk’ and ‘Skin cancer—How to spot the signs and symptoms’. Online randomisation is then performed: those randomised to the control group are thanked for their participation and both groups are given the Cancer Research UK leaflets to take home.

10.1136/bmjopen-2017-017934.supp1Supplementary file 1

#### Intervention group

Participants randomised to the intervention group are assisted with loading the SSM App onto their smartphone by the trial nurse, who continues by giving instructions on its use, supported by written instruction sheets. The core functions of the App, MySkinPal, include full body scan, body diagrams, photo source and browser, information on the signs of melanoma, regular reminders, ability to select moles to share with a doctor and motivation to use including awards/achievements. The nurse ensures that the App’s monthly reminder notification is switched on to prompt each participant regularly. Finally, each intervention participant is given an Apple Apps store/Google Play voucher (up to £5) to pay for the App.

### Outcomes and measures

The primary outcomes of this trial are *consultation rates* for pigmented skin lesions and the *patient interval.* C*onsultation rates* for changes to an existing pigmented skin lesion or concerns about a new pigmented skin lesion for 12 months before the trial and 12 months after the trial consultation will be collected via searching general practice electronic medical records using a clinical notes audit for every participant. The *patient interval* is the time from first noticing a skin change to first consultation. These data will be collected monthly by searches of general practice electronic medical records for all skin changes or pigmented skin lesions presented to their general practitioner (GP) or practice nurse during the 12 months following the trial consultation. When a participant consults about a pigmented skin lesion, they receive a skin questionnaire to complete. This skin questionnaire uses the symptom study instrument modified for melanoma symptoms. The instrument is a participant-completed questionnaire collecting data on symptoms and their duration prior to consultation, validated in prospective studies examining symptom and patient factors associated with longer time to diagnosis for colorectal, lung and pancreatic cancer.^25–27^ The skin questionnaire comprises 10 items starting with a free text response to ‘What was the first skin change or mole you noticed that made you think something might be wrong?’ Each item includes the subitems: ‘When did you first notice this?’ and ‘When did you first tell your GP or nurse?’

Secondary measures and outcomes (measured at baseline, 6 and 12 months) include:
*demographics and clinical variables:* age, gender, marital status, postcode, highest education level, occupation, history of skin cancer (melanoma, squamous cell carcinoma, basal cell carcinoma), skin and hair type (density of freckles on arms before age 20, natural hair colour at age 15, number of severe sunburns aged 2–18), number of raised moles on both arms, measured at baseline only,^21 22^ collected as part of the baseline eligibility assessment;
*sun protection habits scale* developed by Glanz *et al* in the USA for a multicomponent skin cancer prevention programme; this comprises five items measured using a four-point Likert scale, and relating to use of sun protection, sun and sunbed habits, and episodes of sunburn in the previous year,^28^ as we hypothesise that the App reminders will prompt people and reinforce the messages on sun protection;
*skin self-examination benefits and barriers scale:* validated by Manne and Lessin in the USA among melanoma survivors, and developed from previous work on mammography and family members of patients with colorectal cancer.^29^ The benefits scale has seven items (α=0.71) and the barriers scale has 10 items (α=0.74);
*Melanoma Worry Scale (MWS)* validated by Moye *et al* in the USA,^30^ and adapted from the Breast Cancer Worry Scale;^31^ this measure comprises four items, scored 1 to 4, with possible scores ranging from 4 to 17, and higher scores indicating higher levels of worry
*Perceived melanoma risk:* drawn from Manne and Lessin’s measures,^29^ these two items have been widely used for melanoma and other cancer risk assessments to assess estimated percent risk of developing melanoma, and perceived risk compared with a person of the same age (relative risk);
*Self-efficacy for consulting without delay:* A 10-item self-completed scale summed to score 10–100, was used in a primary care trial for lung symptoms and showed good internal reliability (Cronbach α=0.85).^32 33^ It has been adapted for this trial, and reduced to eight items, for example. ‘How confident are you that you can make an appointment to see a doctor when…… you can’t get an appointment with your usual doctor?’;
*Hospital Anxiety and Depression Scale:* This 14-item self-completed scale has been widely used to measure distress and has been extensively validated and shown to perform well in a wide range of populations (mean Cronbach α=0.82; sensitivity and specificity 0.80)^34^;
*12-Item Short Form Survey (SF-12) quality-of-life scale:* a 12-item version of the SF-36 that is widely used and validated to measure functional health and well-being,^35^ for example, ‘During the past 4 weeks, have you had any of the following problems with your work or other regular daily activities as a result of your physical health?… … ’

Other outcome measures include:
*trial feasibility and acceptability*, including data on patient recruitment and attrition rates, reasons for attrition, response rates to skin symptom questionnaires for measuring the patient interval to inform decisions about a future phase III trial;
*melanoma incidence across participating practices* to contextualise trial findings and after 5 years. This will be identified through GP electronic medical records and the National Cancer Registration Service.

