### Statistical analysis

All randomised patients will be considered eligible for inclusion in the analysis in accordance with the intention-to-treat analysis principle. As this is a phase II trial, fully describing and characterising the extent and nature of the missing data is an important part of the analysis. For the outcome analysis, appropriate methods for dealing with missing endpoint data will be informed by a blinded review of the data; however, assuming that this is appropriate, we plan a series of extreme case-sensitivity analyses, where missing data will be replaced with the 2.5th and 97.5th centiles of the non-missing measured outcomes to assess the maximum potential impact on the results of the trial. The baseline characteristics of the two arms will be described using summary statistics. Possible consent bias will be assessed by comparing demographic and clinical variables of participants with those who declined participation, and possible differential attrition will be assessed by comparing baseline characteristics of those who withdraw or die with those who remain in the trial. In addition, we will analyse the missing data to understand the potential impact on the required sample size, and to assess whether and where possible bias may arise, and therefore be minimised, in the future design for the efficacy phase III trial. We will describe the amount (percentage) of missing data in all outcome measures at baseline and follow-up, and evaluate the relationship between missing data and treatment assignment using unadjusted Χ^2^ tests. We will describe whether missing data occur differentially between outcomes. These comparisons will be performed using a two sample t test (or non-parametric equivalent) for continuous variables and Χ^2^ test for categorical variables.

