The primary analysis will be a comparison between the two groups on the consultation rate for skin changes/pigmented skin lesion using a Poisson regression model. Comparisons between groups on binary secondary endpoints will be performed using logistic regression. Comparisons between groups on continuous secondary endpoints will be undertaken using a linear model that includes the baseline value where applicable. A linear model may not be appropriate for the secondary outcome patient interval, as this is expected to be right skewed.^36^ We will explore the nature and extent of the skewness and analyse patient interval using a linear model if possible, adopting other approaches as appropriate, including transformation or categorisation of the patient interval, or methods for statistical inference based on bootstrap resampling. The analyses performed on the primary and secondary endpoints will be repeated adjusting for additional baseline covariates as part of a sensitivity analysis. Point estimates of the intervention effect will be presented with 95% CIs and two-sided P values. Unadjusted P values from secondary analyses will be interpreted in proper context and be clearly labelled.

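### The patient interval is compared only among participants who consult and reply, and may include time before randomisation, so it is not a randomised estimate of the App's effect

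*Protocol article*

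**What the plan says.** **Status.** In the protocol article, Outcomes and measures opens with "The primary outcomes of this trial are" and lists consultation rates and the patient interval. Statistical analysis gives the interval a different status: "A linear model may not be appropriate for the secondary outcome patient interval, as this is expected to be right skewed".

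**Definition.** The interval "is the time from first noticing a skin change to first consultation". The 12-month window after the trial consultation limits when the consultation occurs, not when the change was noticed. Consultations about existing lesions count as well as those about new ones.

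**Who supplies one.** "When a participant consults about a pigmented skin lesion, they receive a skin questionnaire to complete". The instrument is "a participant-completed questionnaire collecting data on symptoms and their duration prior to consultation", and it asks when each change was first noticed. It is sent by post (Measurement timings and study end points). Incomplete return is foreseen, since the feasibility outcomes include "response rates to skin symptom questionnaires for measuring the patient interval to inform decisions about a future phase III trial".

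**Analysis.** The general rule is: "All randomised patients will be considered eligible for inclusion in the analysis in accordance with the intention-to-treat analysis principle". Missing endpoints may be filled in with the 2.5th and 97.5th centiles of the observed values, subject to a blinded data review. For this outcome the plan is to "analyse patient interval using a linear model if possible", with transformation, categorisation or bootstrap as alternatives. Estimates of the intervention effect carry 95% CIs and two-sided P values.

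**Purpose.** The hypothesis at the end of Piloting the intervention is that App users seek help faster once they have noticed a change. Effect estimates are to help choose the phase III primary outcome and, where appropriate, its sample size.

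**The concern.** Randomisation makes the arms comparable as randomised. It does not make those who later consult and reply comparable, and the App is intended to alter who consults. Entry to the interval analysis is therefore itself affected by treatment.

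A separate problem is the start of the clock. A participant who has watched a mole for a year and presents it during the trial contributes that year to the interval, although neither arm could have affected it. If the App brings forward more such lesions, its arm collects more long intervals.

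The only difficulty the analysis section names for this outcome is skewness. Transformation or bootstrap deals with skewness and leaves both problems in place. The interval carries the trial's stated hypothesis, so a biased estimate could mislead the choice of phase III outcome. A larger trial using the same definition would only estimate the same quantity more precisely.

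**Working it through.** **1. The plan's own figure.** The target comes from a recruitment funnel, not a power calculation: 1600 × 0.25 × 0.50 = 200 randomised. This reproduces.

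**2. How many intervals to expect.** The article gives no consultation or reply rate. Assume 5% to 20% consult and 50% to 90% reply:
- Low: 200 × 0.05 × 0.5 = 5 intervals, or 2.5 per arm.
- High: 200 × 0.20 × 0.9 = 36 intervals, or 18 per arm.
- The difference detectable with 80% power at two-sided 5% is 2.80 × √(2/n per arm): about 2.5 SD at the low end and 0.93 SD at the high end.
- Non-consulters number 200 − 40 = 160 to 200 − 10 = 190. Their interval is undefined, not missing. Filling it in would make 80% to 95% of the analysed values artificial.

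**3. A small illustration (all figures assumed).** Ten control consulters have an interval of 60 days.
- In the App arm, ten similar people consult at 45 days, and five more present a lesion noticed 365 days earlier: (10×45 + 5×365)/15 = 152 days. With two extra people: (10×45 + 2×365)/12 = 98 days. The mean is longer although those who would have consulted anyway came sooner.
- If everyone sits at the stated value, the App-arm median is 45 against 60, the right direction.
- A log transformation does not cure the first case: exp[(10 ln 45 + 5 ln 365)/15] = 90 days against 60.
- If three controls also present 365-day lesions, the control mean is (10×60 + 3×365)/13 = 130 days, and most of the gap closes.
- Bias the other way: ten people at 60 days in both arms, plus five extra App participants at 45 days, gives (10×60 + 5×45)/15 = 55 days. The mean shortens although nobody who would have consulted anyway came sooner.

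**4. Simulation (assumed rates, 2,000,000 per arm).** New lesions are noticed at 0.02 per month. The monthly hazard of consulting is 0.15 for new lesions and 0.02 for old ones. Prior duration of old lesions is exponential with mean 12 months. The first consultation within 12 months supplies the interval. The App raises the hazard of consulting in every scenario, so it is truly beneficial.

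| Scenario | Mean, control → App (months) | Median, control → App (months) |
|---|---|---|
| No old lesions, hazard doubled | 3.0 → 2.3 | 2.4 → 1.7 |
| 10% hold an old lesion, hazard doubled | 5.2 → 5.1 | 3.0 → 2.2 |
| 20% hold an old lesion, hazard doubled | 6.8 → 7.1 | 3.6 → 3.0 |
| 20%, hazard ×3 for old and ×1.5 for new | 6.8 → 8.8 | 3.6 → 4.4 |
| Last row, only lesions first noticed after randomisation | 3.0 → 2.6 | 2.4 → 2.0 |

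With 20% holding an old lesion, the hazard doubled and a mean prior duration of 6 months, the mean goes from 5.3 to 5.2, the right direction. Even with no old lesions, the share of each arm contributing an interval differs (12% control, 16% App), so restricting by noticing date does not remove the selection.

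**The case against.** The strongest reply is that the main comparison is safe. Statistical analysis makes a Poisson comparison of consultation rates the primary analysis, and those data come from practice records, not from the questionnaire. The article says clinical outcomes will have limited interpretation, expects no significant clinical conclusions, and promises that unadjusted P values from secondary analyses will be labelled and read in context. Non-return is measured, tested against allocation and given extreme-case analyses. All of this stands and limits the consequence. It does not answer the point: the small-sample caveat concerns imprecision, and the missing-data methods concern values that exist but were not obtained.

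It is also fair that the article nowhere says in words that earlier-noticed changes are included. They are included because the definition sets no limit. A split by noticing date could still appear in an analysis plan not shown here. What the article itself fixes is the definition and the reporting of the comparison as an intervention effect.

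A reader might infer several stronger things that the documents do not support:
- **That the result will be reversed.** This rests on assumed inputs. Controls also receive nurse-guided advice on signs and symptoms, so they too may present old lesions, and medians often keep the right direction.
- **That an ineffective App could look beneficial by prompting early visits.** An App that prompts visits has changed help-seeking. One with no effect on noticing, consulting or replying creates no difference in selection between arms.
- **That the App's photographs and reminders make noticing dates recalled differently by arm.** Nothing in the article bears on this, and no size can be given.

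**Conclusion.** The point holds in a limited form. The interval comparison is made in groups formed after randomisation by an event the App is meant to influence, and it can include time before randomisation. It should not be read as a randomised effect estimate. Both features follow from the article's definition and need no assumed figures.

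The size and direction of the bias cannot be determined from the document. Under the assumed rates, the change in the observed mean ran from a fall of 0.7 months to a rise of about 2 months for an App that was beneficial throughout. Reversal of both mean and median at 20% holding an old lesion appeared when the App was assumed to act more strongly on old lesions than on new ones. The intention-to-treat statement is not false, since it speaks of eligibility for inclusion, but it gives this outcome no protection. It would be wrong to conclude that the trial's primary analysis is compromised: the consultation-rate comparison is unaffected.

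**What to change.** 1. Report the patient interval as a descriptive, non-randomised comparison among consulters who replied, not as a test of efficacy, and give it one status in both sections.
2. Use the noticing date already on the questionnaire to report intervals separately for changes first noticed before and after randomisation. Make the latter the main summary, and state that it is still selected on consulting.
3. Do not apply the 2.5th/97.5th centile fill-in to non-consulters. Keep it, if used at all, for consulters who did not return the questionnaire.
4. Optionally, add time from randomisation to first pigmented-lesion consultation in all randomised participants, as a supporting randomised analysis from the records already audited, with censoring at formal withdrawal. State that it measures consulting, not speed after noticing: people who never noticed a change count as not having consulted. It therefore cannot replace the interval as a test of the stated hypothesis.

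The cost is analysis-plan wording, one split of existing data and, if wanted, one extra analysis. The interval loses its standing as a causal effect estimate, and the post-randomisation subset is smaller than an already small set. The change should be settled before the arms are compared. The steering committee, which is to approve the data analysis plan, can do this.
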